**Fig. 2 Fig2:**
[figure not shown]
Overview of physical therapist participant flow through the study

### Data collection and management

Data will be obtained through questionnaires hosted on a secure online survey platform (REDCap 10.9.4, Vanderbilt University, US). At each testing period knee injury participants will also attend a 1-h in-person laboratory session to complete computerized dynamometry testing of knee extensor and flexor muscle function, and a dual x-ray absorptiometry scan to estimate body mass index and body composition. At the end of the in-person session, participants will be given a triaxial accelerometer and instructed on how to wear it for 7-days. The accelerometer will be returned in a postage paid courier envelope. Secure online forms (Microsoft© Sharepoint) will be used to track knee injury participants attendance, adverse events, healthcare use, exercise/activity goal completion, Rating of Perceived Effort, and any associated pain. Data will be stored in secure electronic databases and de-identified. All authors will have access to the final dataset.

### Randomization allocation, concealment and blinding

After baseline testing, knee injured participants will be randomly assigned to IG or 10-week DG groups in a 1:1 allocation ratio, stratified on sex in variable block sizes [4, 6, 8]. A research coordinator will use serial labelled opaque envelopes prepared by a statistician (blind to data collection and daily trial activities) with a randomization schedule (SAS v9.4) to reveal group assignment.

The nature of the intervention does not allow for full blinding (i.e., participants and PTs cannot be blinded to study group). To reduce allocation bias, participants will be randomized to study groups by a research coordinator using serial labelled opaque envelopes prepared by our statistician (no interaction with participants and blind to data collection and daily trial activities). To reduce confirmation bias, persons leading outcome assessment and analyses will be blinded to group allocation, and participants will be asked not to disclose allocation to assessors. All questionnaires are self-reported (assessor blinded). Participants will also be blinded to study hypotheses.

### Intervention

The intervention is a virtually-delivered PT-guided knee health program called SOAR (Stop OsteoARthritis). The program has 3 components: 1) one-time Knee Camp; 2) individualized weekly home-based exercise-therapy, physical activity and tracking, and; 3) weekly 1:1 PT-guided exercise-therapy and activity action-planning with optional online group exercise class. Before starting, participants will recieve a Fitbit Inspire® activity tracker (Google LLC), workbook (educational materials), and resistance loop set (Chimaera®) providing up to 100 pounds of resistance to enable exercise progression.

#### Knee camp

This two-hour session, conducted over videoconferencing (Zoom®) includes a 1-h interactive group-based education session, 1:1 knee exam and exercise-therapy and physical activity goal-setting with a PT. The education session covers topics approved by patient partners, consistent with shared decision making theory, [29] clinical guidelines [41] and current understanding of OA (Table 1, Supplementary File 1 - Education session content). These concepts will be reinforced across the program. During the knee exam, PTs and participants co-identify and prioritize functional limitations. Exercise-therapy and activity goal-setting followed a Brief Action Planning (BAP) [23] approach (Fig. 1, Supplementary File 1 - BAP overview). Briefly, PT’s guide participants to identify at least one individualized home-based exercise-therapy and one physical activity SMART (*specific*, *measurable*, *attainable*, *relevant*, and *time-bound*) goal with tasks and adequate dose (target Rating of Perceived Effort [45] to address their unique functional limits (Table 2, Supplementary File 1 - Exemplar SMART Goals) for week 1. Participants can use the resistance band kit, body weight, common household materials (i.e., furniture, stairs) or any exercise equipment that they had access to when developing their dose. Goals will be modified until participant’s confidence to execute them rates ≥ 7/10. Actions to address perceived barriers will also be discussed. Participants will be instructed to wear it 24-h/day and share their Fitbit® activity ‘Dashboard’ with researchers. Finally, participants will be orientated to a Participant-Tracking form, where they will record their week 1 exercise-therapy and physical activity goals.

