### Procedures

Figure 1 outlines the study phases for participants with a past knee injury. Interested persons will be directed to an online screening survey (Qualtrics XM, US) and those potentially eligible will be emailed study information and scheduled for a videoconferencing interview to confirm eligibility. Eligible persons will receive an URL to an electronic consent form located on a data management platform (REDCap 10.9.4, Vanderbilt University, US). After consenting, participants will complete baseline testing and be randomly allocated to study group (see below). The immediate study group (IG) will be complete an 8-week (weeks 1–8) SOAR program (Knee Camp, home-based exercise-therapy and physical activity with tracking, weekly 1:1 PT counseling sessions, and optional weekly group-based exercise classes) followed by an additional 8 weeks (weeks 10–17) of home-based exercise-therapy and physical activity with tracking, weekly 1:1 PT counseling sessions, and optional weekly group-based exercise classes. In contrast, after a 10-week delay, the delayed study group (DG) will complete an 8-week (weeks 10–17) SOAR program (Knee Camp, home-based exercise-therapy and physical activity with tracking, weekly 1:1 PT counseling sessions, and optional weekly group-based exercise classes). Knee injury participant outcomes will be evaluated at baseline (T0), 9-weeks (T1-primary endpoint to assess efficacy), and 18-weeks (T2- endpoint to inform optimal intervention length).

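### Assessor blinding at the week-9 strength test is not protected against a likely visible cue, the Fitbit issued with the programme

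*Protocol article*

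**What the plan says.** The Intervention section of the protocol article describes the programme's three components and then the kit: "Before starting, participants will recieve a Fitbit Inspire® activity tracker", together with a workbook and resistance loops. The wear instruction is given at Knee Camp, the opening session of the programme: "Participants will be instructed to wear it 24-h/day". No exception for laboratory visits is stated.

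Under Procedures, the immediate group has the programme in weeks 1–8, "followed by an additional 8 weeks (weeks 10–17) of home-based exercise-therapy and physical activity with tracking". For the other arm, "after a 10-week delay, the delayed study group (DG) will complete an 8-week (weeks 10–17) SOAR program". The primary endpoint, T1, is at 9 weeks.

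Strength is measured face to face. Data collection and management says "At each testing period knee injury participants will also attend a 1-h in-person laboratory session", and dynamometry is done there. On blinding, the Randomization section says "persons leading outcome assessment and analyses will be blinded to group allocation, and participants will be asked not to disclose allocation to assessors". The abstract calls the trial assessor-blinded.

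**The concern.** Taken together, these sections suggest that at T1 one arm has been told to wear a study-issued device round the clock and the other has probably not received it. An assessor who notices the device, and knows when it is issued, could guess the group at the visit that supplies the primary outcome. The stated safeguard concerns what participants say, not what they wear.

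The primary outcome is peak torque over three repetitions of a strength test. As general reasoning, and not from any figure in the documents, results of a maximal-effort test can depend on how the assessor runs it. Participants and physiotherapists know the allocation, so blinding the person who takes the measurement is an important protection against detection bias here.

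**Working it through.** The point is mainly a matter of timing, so the sections are set side by side by visit.

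- **T0 (baseline).** Randomisation follows baseline testing (Procedures; Randomization section). Neither group has started the programme, so there is no arm-specific cue.
- **T1 (week 9).** The immediate group has had Knee Camp, the wear instruction and weeks 1–8 of the programme. Physiotherapists ask about Fitbit wear each week (Weekly PT-guided section). The group resumes with tracking in week 10, so it can be expected to keep the device. The delayed group's Knee Camp falls in weeks 10–17. Study design and setting gives the delay as 9 weeks and Procedures gives 10, but on either figure the programme starts no earlier than the T1 time point.
- **T2 (week 18).** Both groups have been through Knee Camp, so a study tracker no longer separates the arms.

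The asymmetry is thus confined to T1. Every contrast listed for the primary outcome in Statistical analyses uses a T1 value: IG T1–T0 versus DG T1–T0; DG T2–T1 versus T1–T0; and IG T1–T0 versus DG T2–T1.

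**How many participants.** Allocation is 35 per group, so at most 35 of 70 carry the cue. With the 25% attrition in Sample size, 35 × 0.75 = 26.25, or about 26.

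**The plan's own figure.** No stated figure depends on this point, but the sample size supplies the SD used below. With difference 0.22, SD 0.25, two-sided α 0.05 and power 0.80:

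n per group = 2 × (1.96 + 0.8416)² × 0.25² / 0.22² = 20.3, rounded up to 21, or 42 in all, as stated.

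**Sensitivity to an assumed bias.** The documents give no estimate of assessor bias, so b below is purely assumed: a net between-group shift in favour of the immediate group, with no true effect.

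SE = 0.25 × √(2/26) = 0.0693 Nm/kg

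Two-sided rejection rate = Φ(b/SE − 1.96) + Φ(−b/SE − 1.96)

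| Assumed b (Nm/kg) | Rejection rate (nominal 5%) |
|---|---|
| 0.02 | about 6% |
| 0.05 | about 11% |
| 0.08 | about 21% |
| 0.11 | about 36% |

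This shows only how a given bias would act at this sample size. It is no evidence that any such bias is present.

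**The case against.** A reader might infer that assessor blinding fails at T1 and that the abstract's assessor-blinded label is unsupported. The documents do not support that, for these reasons.

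- **The delayed group's lack of a device is inferred.** The timing of issue could mean before starting the study, and refusal to wear an activity tracker is an exclusion for everyone (Participants). The programme reading is still the more natural one: the sentence follows the list of programme components, and the wear instruction comes only at Knee Camp. Had the delayed group worn the device from baseline, it would have received a programme item in a waiting period that Study design and setting justifies by usual care being no care. Either reading needs a clarifying sentence.
- **Wear and visibility at the visit are inferred.** T1 falls between the two immediate-group blocks, and the article does not say whether the device is worn in that gap. Nor does it say where on the body it is worn, so one cannot claim that it would be in plain view.
- **A consumer tracker is a cue, not proof of allocation.** Delayed-group participants may own one, and the assessor may not know which devices are study-issued or when.
- **Assessor blinding is not the only blinding.** Those leading the analyses are also blinded, and participants are blinded to the hypotheses. The computerised dynamometer at a fixed speed also limits discretion to some degree.
- **Visit-day handling may be in the full protocol or a testing manual.** That is possible, and an omission alone would not be a finding. Here, however, the article names its safeguard for the visit, that safeguard misses this cue, and another section gives an unqualified wear rule that tends to create it.

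These objections reduce the strength of the claim and the confidence in it. They do not remove the gap between the wear instruction and the stated safeguard.

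**Conclusion.** The point holds in limited form, with moderate confidence. Followed as written, the plan makes an arm-specific visible cue likely at the primary-endpoint strength test, and the one safeguard described for that visit does not address it. At most the 35 participants of the immediate group would carry the cue, or about 26 after the planned attrition. The resulting bias cannot be sized from the documents and may be nil.

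The conclusion assumes that the Fitbit is issued around the start of each group's programme, that immediate-group participants still wear it at T1, and that the assessor can see it and knows what it signifies. The first two are likely from the schedule; the third is not established. This is a cheap improvement and not a defect that invalidates the primary comparison.

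**What to change.** In Data collection and management, or in the Randomization section, state that before meeting the assessor at every laboratory visit (T0, T1 and T2) participants in both groups take off any activity tracker, study-issued or their own, and put away programme material. The research coordinator opens the allocation envelopes and so already knows the groups; the coordinator should put this in the appointment reminder and check it on arrival. In Knee camp, exempt test visits from the 24-hour wear instruction.

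The cost is a sentence in each place, a line in the reminder and about one hour of Fitbit data per visit. No primary or secondary outcome uses those data: physical activity as a secondary outcome comes from the separate waist-worn Actigraph, which is handed out at the end of the session.

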#### Weekly home-based exercise-therapy, physical activity and activity tracking

At home, participants will work to meet their exercise-therapy and physical activity goals. Degree of exercise-therapy goal completion, Rating of Perceived Effort, and any associated pain will be recorded on the Participant-Tracking form, and physical activity (Fitbit®) data synchronized with the Fitbit® online ‘Dashboard’.

#### Weekly PT-guided exercise-therapy and physical activity action-planning

Each week knee injury participants will attend a short (~ 15–30) 1:1 virtual PT counseling session and have the option of supplementing their home program with a regularly scheduled one-hour virtual PT-guided group exercise class (Table 3, Supplementary File 1 - Group exercise class menu). At the weekly counselling sessions PTs will ask and record responses to questions related to adverse events, medication and healthcare use, Fitbit® wear, and SMART goal completion on a bespoke PT tracking form. Participants and their PT will progressively modify or add SMART exercise-therapy and physical activity goals (using a BAP approach) based on the past weeks goal completion, physical activity (Fitbit® Dashboard), symptoms and obstacles encountered. At group class, participants will receive added instruction and feedback about exercise performance and progression. Participants will be able to email their PT between sessions as needed.

### Physiotherapist training

Prior to delivering the intervention, registered musculoskeletal PTs will complete BAP training and certification (8 h), and SOAR training (6 h) (Table 4, Supplementary File 1 – SOAR PT Training). BAP skills training and certification will be conducted in coordination with the Centre for Collaboration, Motivation and Innovation (Canada). BAP Certification (1-h role-play scenario) will follow a 4-h online course and three, 1-h group practice and feedback sessions. During the SOAR training, PTs will be oriented to the theoretical foundations underpinning the intervention, Knee Camp educational content, and observe and practice a virtual knee exam and SMART goal setting with a simulated patient followed by a group debrief. PTs will also be instructed in how use Zoom®, best-practice for virtual rehabilitation, [46] communication with knee injury participants, research ethics principles and how use an online PT Tracking form.

### Outcomes

Table 1 outlines study outcomes and measurement timepoints. The primary and secondary outcome choices are based on feasibility study data, [31] considered relevant by patient partners, and reliable and valid. Exploratory outcomes will be collected to assist in optimizing the effect and length of the intervention and determine which components are essential for efficacy and those that can be adapted for implementation.

**Table 1 Tab1:**
[figure not shown]
Schedule of Enrolment, Interventions and Assessments

Er (enrollment), T0 (allocation), T1 (primary end point), T2 (end point to inform optimal intervention length), End (end of study)

*CARE* Consultation and Relational Empathy Measure, *EARS* Exercise Adherence Rating Scale, *GLTEQ* Godin Leisure Time Exercise Questionnaire, *KOOS* Knee injury and Osteoarthritis Outcome Score, *MDSPS* Multi-Dimensional Scale of Perceived Support Scale, *mo* month, *PASSQ* Perceived Available Social Support Questionnaire, *PHS* Partner and Health Scale, *QOL* Quality of Life, *SR* Sport and Recreation, *TSK* Tampa Scale of Kinesiophobia

Protocol feasibility outcomes will be collected to inform the design of a future hybrid effectiveness-implementation RCT.

#### Participant characteristics

Age, gender (woman, man, gender-diverse, trans-gender, other), sex (female, male, intersex), ethnicity, current employment status, education attained, sport participation (main pre-injury sport, return-to-sport, participation in last year), and injury history (injury age, injury type, time since injury, treatment received, subsequent injury) will be collected with a baseline questionnaire. Participants were asked to answer all questions in reference to the study knee injury, or in the case of bilateral knee injuries, the most symptomatic.

#### Primary outcome

##### 9-week change in normalized peak knee extension torque

Quadriceps weakness is an established independent risk factor for OA illness, [47] and deficits in quadriceps function persist for years beyond knee trauma [11, 48]. In a recent meta-analysis quadriceps weakness was associated with increased odds of symptomatic knee OA in women (OR 1.85, 95%CI 1.29,2.64) and men (1.43, 1.14,1.78) [49]. Isokinetic concentric and eccentric knee extension torque will be assessed on computerized dynamometer (Biodex, System 4™, Biodex Medical Systems Inc. USA) at 60 degrees/sec over 0–100 degrees [50]. The peak torque reached over 3 repetitions will be recorded and normalized to body mass (Nm/kg).

#### Secondary outcomes

##### 9-week change in average daily MVPA

Inactivity increases OA risk [18] and physical activity attenuates adiposity 3–10 years after knee injury [10]. Average daily MVPA physical activity will be assessed with a waist-worn triaxial accelerometer (Actigraph™ GT3XP, Actigraph USA). Participants will be asked to wear the device in the correct orientation over the right anterior superior iliac spine (waist-worn) for a period of 7-continuous days, only removing for water/bathing or activities that may damage it. Participants will complete a monitor wear log to record non-wear times, including the duration and intensity (i.e., light, moderate, or vigorous) of activities performed when the device was not worn. Physical activity data will be included if the wear period exceeded ≥5 days (including at least one weekend day), with ≥10 h of data recorded per day. Using ActiLife™ software (version 6.1), raw acquisition data will be extracted in 10-s epochs using the Low Frequency Extension parameter. Wear time will be validated using the Choi algorithm (2011) [51] and cross-referenced with the self-reported monitor wear-log, and the Troiano algorithm^21^ will be used to categorize MVPA.

##### 9-week change in self-reported knee-related self-efficacy

Self-efficacy, or one’s belief in their ability to organize and execute actions to manage a prospective situation, [52, 53] predicts health behaviour including exercise participation [54]. The 19-item Knee Self-efficacy Scale (KSES) [55] will be used to measure self-reported knee-specific self-efficacy. Each item is scored on an 0–10-point Likert scale, with 0 indicating no knee-related self-efficacy and 10 indicating full knee-related self-efficacy. Individual item scores are summed and divided by 19 to produce a total score ranging from 0 to 10 (0 representing poor knee-related self-efficacy and 10 representing full knee-related self-efficacy).

##### 9-week change in self-reported knee-related QoL

Patient partners identify QoL as the most relevant outcome and people with an activity-related knee injury face reduced QoL for up to 10-years [11]. The 5-item QoL subscale of the Knee Injury and Osteoarthritis Outcome Score (KOOS) questionnaire will be used to measure self-reported knee-related QoL. Each item is scored on an 0–10-point Likert scale, with 0 indicating no knee-related QoL and 10 indicating full knee-related QOL. Individual item scores are summed and transformed to a score out of 100 (0 representing poor knee-related QoL and 100 representing full knee-related QoL).

#### Exploratory outcomes

In addition to the outcomes listed below, the 18-week change in primary, secondary and exploratory outcomes will be measured in participants allocated to the IG to inform optimal intervention length.

##### 9-week change in self-reported knee-related pain, symptoms and function in sport and recreation

The 8-,18- and 5-item symptom, pain, function in sport and recreation subscales of the KOOS questionnaire will be used to measure self-reported knee-related pain, symptoms and function in sport and recreation [56]. Each item is scored on an 0–10-point Likert scale, with 0 indicating many symptoms and 10 indicating no symptoms. Individual item scores are summed to produce a total score. Higher scores indicate lower levels of knee-related pain and symptoms, and higher levels of knee-related sport and recreation function.

##### 9-week change in self-reported patient-specific overall function

The 3-item Patient Specific Functional Scale will be used to identify, quantify and assess changes in functional limitations that are most relevant to participants [57]. This scale prompts participants to identify three activities important to them and rate their ability to perform each activity on a 10-point numerical rating scale. Individual scale scores are summed and transformed to a 0–100 scale with higher scores indicating better outcomes.

##### 9-week change in self-reported physical activity

The 4-item Godin Leisure Time Questionnaire will be used to measure self-reported physical activity [58]. Using the number of 15-min bouts of mild, moderate, and strenuous physical activity a participant engages in over a typical seven-day period weekly metabolic equivalents of physical activity are calculated.

##### 9-week change in self-reported perceived self-care

The 12-item Partner in Health Scale will be used to measure perceived self-care (active involvement to self-manage an ongoing condition) [59]. Each item is scored on a 9-point scale. Scores on individual items are summed to produce a total score with lower scores indicating better ability to manage their knee health.

##### 9-week change in self-reported knee-related fear of movement and re-injury

The 11-item Tampa Scale of Kinesiophobia will be used to measure self-reported fear of movement and re-injury [60]. Each item is scored on a Likert-scale from strongly disagree to strongly agree. The item scores are summed to produce a total score with a high value indicating a high degree of fear.

